### Interim analyses {21b}

An interim analysis will be performed by a data and safety monitoring board (DSMB) for the primary outcome measure after the inclusion of 50 patients. O’Brien- Fleming stopping criteria will be used for the primary outcome (24). If the *p* value is lower than 0.0107 for inferiority of fosfomycin to ciprofloxacin at the 5% margin, the DMSC may recommend early termination of the trial. Accrual will not be suspended for these monitoring and analysis.

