### Sample size {14}

The reviewed clinical trials and meta-analyses have consistently shown that 65% of patients receiving prophylactic the fluoroquinolones levofloxacin and ciprofloxacin will develop infectious fever (2,17,18) which is consistent with success rate of 35%. Considering that the actual rate of resistance to fluoroquinolones is established to be around 50%, we anticipate a success rate of 17% and 30% in the active control and active and experimental control arms, respectively.

If a non-inferiority margin of 5% is defined, one hundred and thirty-four patients (67 in each arm) will be needed to demonstrate non-inferiority of fosfomycin versus ciprofloxacin with 80% potency and an alpha level of 0.05.

Considering that 15% of the enrolled patients will be ineligible or unable to be evaluated, the maximum number of study participants will be 156: 78 patients in each arm.

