### Composition of the data monitoring committee, its role and reporting structure {21a}

A meeting will be held by non-study personnel to evaluate the results of 80 patients. The interim analysis committee will be composed of a hematologist, a microbiologist and a clinical pharmacologist.

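### The interim look is set at 50 patients in one section and 80 in another, and the stated threshold of 0.0107 is not an O'Brien-Fleming boundary at 50

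*Protocol article*

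**What the plan says.** Interim analyses {21b} schedules one analysis by the data and safety monitoring board "for the primary outcome measure after the inclusion of 50 patients". It names O'Brien-Fleming criteria and allows the board to advise stopping if the p "value is lower than 0.0107 for inferiority of fosfomycin to ciprofloxacin at the 5% margin". It gives no sidedness and no information fraction.

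Composition of the data monitoring committee {21a} states: "A meeting will be held by non-study personnel to evaluate the results of 80 patients". It continues: "The interim analysis committee will be composed of a hematologist, a microbiologist and a clinical pharmacologist". It does not mention 50 patients, and {21b} does not mention 80.

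The planning figures are in Sample size {14}: "we anticipate a success rate of 17% and 30% in the active control and active and experimental control arms, respectively", and "If a non-inferiority margin of 5% is defined, one hundred and thirty-four patients (67 in each arm) will be needed", with 80% power and alpha 0.05. The same section cites a historical fluoroquinolone success rate: "which is consistent with success rate of 35" per cent. Statistical methods {20a} tests the final comparison at two-sided 0.05. Trial status reports 106 patients recruited at submission.

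**The concern.** Two sections describing the same independent review give different patient counts. An O'Brien-Fleming boundary depends on the fraction of information available at the look, so the count and the threshold have to agree. If the look is at 50, a threshold of 0.0107 is not the boundary named. If it is at 80, the threshold is about right and the section stating it gives the wrong count.

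The hypothesis is also unclear. The sentence can mean stopping because fosfomycin is shown to be worse by more than 5 points, or stopping because the null of inferiority is rejected, which is an early claim of non-inferiority. The first is a safeguard for patients. The second spends type I error. A board could not apply the sentence without first choosing between them.

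**Working it through.** **Inputs.** Look at 50 ({21b}) or 80 ({21a}). Evaluable N 134 and maximum N 156 ({14}). Success 17% on ciprofloxacin and 30% on fosfomycin, margin 5 points ({14}). Threshold 0.0107 ({21b}).

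**Which alpha reproduces the plan's N.** n per arm = (z_alpha + z_beta)² × [p_C(1−p_C) + p_F(1−p_F)] / (p_F − p_C + margin)².
- The variance term is 0.17×0.83 + 0.30×0.70 = 0.3511, and the denominator is 0.18² = 0.0324.
- One-sided 0.05: (1.645 + 0.842)² × 0.3511 / 0.0324 = 67.0, so 67 per arm. This matches the plan.
- One-sided 0.025: 85.05, so 86 per arm. This does not match.

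**O'Brien-Fleming boundary, two looks.** Information fraction t = look/N. Classical form: Z1 = c/√t, with c solved so that the overall error is 0.05. Spending form, one-sided: p1 = 2[1 − Φ(z_{alpha/2}/√t)]; for two-sided 0.05, the same formula is applied at 0.025 in each tail and doubled. In the table, p is one-sided in the one-sided columns and two-sided in the two-sided columns.

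| Look | t | Classical, one-sided 0.05 | Classical, two-sided 0.05 | Spending, one-sided 0.05 | Spending, two-sided 0.05 |
|---|---|---|---|---|---|
| 50/134 | 0.373 | 0.0033 | 0.0013 | 0.0013 | 0.0005 |
| 50/156 | 0.321 | 0.0018 | 0.0005 | 0.0005 | 0.00015 |
| 80/134 | 0.597 | 0.0142 | 0.0099 | 0.0112 | 0.0074 |

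Example, 50/134 classical one-sided: c = 1.658, √0.373 = 0.611, Z1 = 2.715, p = 0.0033. The most lenient reading at 50 takes this one-sided boundary as a two-sided p: 2 × 0.0033 = 0.0066. None of these reaches 0.0107.

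With sidedness read consistently, 0.0107 belongs to t between 0.54 and 0.65, or about 72 to 87 of 134. By the spending form at one-sided 0.05 it is t = 0.590, or 79 patients.

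**Read as an inferiority stop.** Z = (p_C − p_F − 0.05)/SE, Wald, one-sided p < 0.0107. With 25 per arm, about 0.17 × 25 = 4 ciprofloxacin successes are expected. With no fosfomycin success:
- 4 successes: Z = (0.16 − 0.05)/0.0733 = 1.50, p = 0.067
- 6 successes: p = 0.013
- 7 successes: p = 0.005, the first count that stops

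Stopping probability by exact binomial enumeration:

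| Ciprofloxacin / fosfomycin success | 50 patients | 80 patients |
|---|---|---|
| 17% / 12% (deficit equals margin) | 0.9% | 1.1% |
| 17% / 7% | 2.6% | 5.2% |
| 17% / 0% | 11.8% | 36.8% |
| 35% / 20% | 7.7% | 11.2% |
| 35% / 10% | 30% | 49% |
| 35% / 5% | 52% | 78% |

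**Read as early non-inferiority.** Under the planned rates the chance of stopping at 50 is about 24%. With 0.0107 at 50/134 and an unadjusted final test, total one-sided error is 0.0555 (final 0.05) or 0.032 (final 0.025). At 80/134 it is 0.053 or 0.030, so part of the excess comes from leaving the final test unadjusted.

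**The case against.** The strongest reply is that there is only one slip. If 80 is the intended look, the planned alpha gives 0.0112 against the stated 0.0107, so the threshold is essentially right and only the count in {21b} is wrong. This largely stands and points to the likely repair. It remains an inference: the protocol does not say which number governs, and the match is not unique. If a classical one-sided 0.05 boundary is quoted as a two-sided p, 0.0107 would fit t = 0.426, about 57 of 134.

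A reader might infer more than the documents support:

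- **That the rule cannot fire.** It can. The low figures rest on 17% control success. At the historical 35%, it stops 30% to 52% of trials at 50 patients for deficits of 25 to 30 points.
- **That the threshold is 3 to 20 times too lax.** That range (0.0107/0.0033 to 0.0107/0.0005) leaves out the mixed reading, where the factor is 0.0107/0.0066 = 1.6.
- **That false non-inferiority claims are inflated.** A stop for inferiority alone cannot do this, and the board's advice is not binding. Tightening the threshold at 50 would weaken the safeguard further: for 0% against 17%, stopping falls from 11.8% at 0.0107 to 5.0% at 0.0033.
- **That a futility rule is missing.** The protocol claims none. With 106 patients recruited, past both counts, a new one at 80 could not be prospective.

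It might also be said that 50 and 80 are two separate reviews. No text describes two looks, and {21a} calls its group the interim analysis committee.

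**Conclusion.** The point stands on two errors on the page: 50 against 80 patients, and a threshold that no standard two-look O'Brien-Fleming form gives at 50 of 134 (0.0005 to 0.0033, at most 0.0066) or at 50 of 156. It must be corrected because it concerns a decision rule on the primary outcome, and correcting it is cheap.

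The effect on type I error is conditional: none if the rule stops only for inferiority, some if it is an early non-inferiority claim. The weakness as a safeguard is a secondary observation and depends on 17% control success and a one-sided Wald test. The boundary figures assume a single interim look and information proportional to patients with a known outcome.

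**What to change.** - State one interim size, the same in {21a} and {21b}, counted in patients whose primary outcome is known.
- State the hypothesis tested (inferiority beyond the margin, or rejection of inferiority) and whether the p value is one- or two-sided.
- Recompute the boundary for that information fraction and name its form. At 80/134 with one-sided 0.05, the alpha that reproduces N = 134, the spending form gives about 0.0112. If early non-inferiority is meant, give the matching final critical value as well.
- Tell the board how often the rule would stop under the planned rates, so that not crossing the boundary is not over-read.
- Record which look was held and which threshold was applied, since recruitment has passed both counts.

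The cost is wording in the protocol and the board's charter, plus one line of record. No added patients and no futility rule are needed. If the test is for early non-inferiority, the final test becomes slightly stricter.

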### Methods for additional analyses (e.g., subgroup analyses) {20b}

There is no planned sub-group analysis.

### Methods in analysis to handle protocol non-adherence and any statistical methods to handle missing data {20c}

To prevent attrition bias, two types of analysis will be performed: an intention-to-treat analysis, in which all randomized patients will be analyzed according to the group to which they were randomized, regardless they received the assigned treatment or not, and, in addition, a per-protocol analysis will be performed in all randomized patients who finally received the assigned treatment for at least of 24 h (2 doses of ciprofloxacin and 3 doses of fosfomycin).

The imputation of missing variables will consider the distribution of the variables, the allocation group, the center, and the baseline condition (acute leukemia or stem cell transplant).

The method of fully conditional specification (FCS) using the MI procedure of SAS, version 9.4 (SAS Inc, Cary, NC, USA), will be used [15]. In this method, FCS imputations are generated sequentially by specifying an imputation model for each variable given the other variables. Ten imputations will be used in the imputation model and sensitivity analysis will be performed.

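### Ten imputations is a low number for a verdict read from one confidence limit: if primary outcomes are imputed, that limit carries avoidable seed noise, which at least 100 imputations would largely remove

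*Protocol article*

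**What the plan says.** Section {20c} of the protocol article plans an intention-to-treat analysis that keeps every randomised patient in the assigned arm, and a per-protocol analysis beside it. It then describes imputation by fully conditional specification in SAS: "The imputation of missing variables will consider the distribution of the variables, the allocation group, the center, and the baseline condition" (acute leukaemia or transplant). The number is fixed: "Ten imputations will be used in the imputation model and sensitivity analysis will be performed".

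The Statistical methods section {20a} analyses febrile neutropenia in both populations and promises the difference in proportions with a 95% confidence interval. The Sample size section {14} sets the margin and the evaluable number: "If a non-inferiority margin of 5% is defined, one hundred and thirty-four patients (67 in each arm) will be needed". It also allows for "15% of the enrolled patients will be ineligible or unable to be evaluated", which raises the total to 156, or 78 per arm.

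The article gives no expected rate of missing primary outcomes. It does not say in so many words that the primary outcome will be imputed.

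**The concern.** Multiple imputation is itself a simulation. A run with another seed gives another pooled estimate, another between-imputation variance and so another confidence limit. Ten imputations are usually enough for a point estimate. Here, though, a yes-or-no conclusion depends on one limit set against a narrow margin, and that limit picks up noise from both the estimate and the estimated variance.

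If the limit falls close to the margin, two competent analysts following the stated procedure on the same data could report different conclusions. This noise does not come from the patients, and more imputations reduce it almost for free. The article fixes the number itself, so this is not a detail left open for the analysis plan.

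**Working it through.** **Inputs**
- Planning success rates, from Sample size {14}: "we anticipate a success rate of 17% and 30% in the active control and active and experimental control arms, respectively", that is 17% for ciprofloxacin and 30% for fosfomycin.
- Margin 5 points, 67 evaluable and 78 randomised per arm (same section).
- 95% confidence interval, from {20a}. Ten imputations, from {20c}.
- Share of outcomes missing: not given. Assumed 1% to 15%, missing at random, equal in both arms.

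**The plan's own figure.** n per arm = (0.17×0.83 + 0.30×0.70) × (1.645 + 0.842)² / (0.13 + 0.05)² = 0.3511 × 6.183 / 0.0324 = 67.0. The stated 67 per arm is reproduced with a one-sided alpha of 0.05.

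**Seed noise by formula.** Write f for the missing share and m for the number of imputations.
- Complete-data variance at 78 per arm: W = 0.3511/78 = 0.00450, so the standard error is 6.7 points.
- Between-imputation variance: B = W × f/(1−f).
- Seed noise of the pooled estimate: a = √(B/m).
- Total variance: T = W + (1 + 1/m)B.
- Seed noise of the limit through the estimated B: b = 1.96 × (1 + 1/m) / (2√T) × B × √(2/(m−1)).
- Seed-to-seed SD of the lower limit: approximately √(a² + b²).

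At f = 15%, m = 10: B = 0.000794, a = 0.89 points, √T = 7.33 points, b = 0.55 points, and √(0.89² + 0.55²) = 1.05 points.

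At f = 5%, m = 10: B = 0.000237, a = 0.49, √T = 6.90, b = 0.17, giving 0.52 points.

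At f = 1% and 2%, m = 10, the same steps give 0.22 and 0.31 points.

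At m = 100 they give 0.16 points (5%) and 0.32 points (15%).

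**Seed noise by simulation.** 1,500 data sets with 200 seeds each; beta-binomial imputation within arm; Rubin's rules with t limits; 17% versus 30%. With 78 per arm, the nominal 2%, 5%, 10% and 15% are 2, 4, 8 and 12 missing patients per arm.

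| Missing | m | SD of lower limit (points) | Two seeds disagree at −5 |
|---|---|---|---|
| 2% | 10 | 0.36 | 2.2% |
| 5% | 10 | 0.53 | 2.8% |
| 10% | 10 | 0.82 | 4.5% |
| 15% | 10 | 1.09 | 5.5% |
| 5% | 50 | 0.23 | 1.0% |
| 15% | 50 | 0.47 | 2.5% |
| 5% | 100 | 0.17 | 1.1% |
| 15% | 100 | 0.33 | 1.8% |

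Formula and simulation agree. A separate simulation gave 0.52 and 1.07 points at m = 10, and 0.16 and 0.31 at m = 100, for 5% and 15% missing.

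**How often the seed matters at all.** With m = 10, between 1% and 99% of seeds favour non-inferiority in 11% of data sets at 5% missing and in 24% at 15%. With m = 100 these shares are 4% and 7%. If the true rates are equal, at 17% or at 35%, two seeds disagree in about 1 to 3% of trials at m = 10.

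**Does the confidence level matter?** With a 90% interval, which would match the alpha that reproduces 67, b at 15% missing becomes 0.55 × 1.645/1.96 = 0.46 and the SD √(0.89² + 0.46²) = 1.00 point. The noise is nearly the same.

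**The case against.** The case for leaving ten alone has four parts.

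*The noise is small beside sampling error.* This is correct. Adding 1.09 points to 6.7 in quadrature gives √(6.7² + 1.09²) = 6.79, about 1% more. The estimate loses about 1.5% efficiency at 15% missing information, since 1/(1 + 0.15/10) = 0.985. At the planning rates the mean lower limit is about −0.7 (5% missing) to −1.4 (15%), some 4 points clear of −5. Ten imputations is therefore not a mistake.

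*Missing outcomes may be rare.* This also stands. The 15% in the Sample size section counts ineligible patients too and serves only to inflate the sample. Section {20a} confines intention to treat to eligible randomised patients, while {20c} takes all randomised patients. Patients stay in hospital during prophylaxis {11c}, and fever and neutrophil counts are fully checked at monitoring {23}. At 1 to 2% missing, the SD is only 0.2 to 0.4 points.

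*The outcome may not be imputed at all.* Section {20c} speaks of variables in general, and the logistic models in {20a} use baseline characteristics that could be what is meant. However, {20c} offers no other rule for a missing outcome in a population that keeps everyone randomised.

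*More imputations do not abolish disagreement.* True: about 1 to 2% of seed pairs still differ at 100. A seed fixed beforehand removes any choice between runs, and its absence from an article is ordinary programming detail.

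Two stronger readings are tempting. A reader might infer that entering centre, with 11 hospitals and about 156/11 = 14 patients each, makes the imputation break down where no success was observed. The article says only that centre will be considered and does not specify plain logistic imputation with a term for each hospital. Simulated seed noise is practically the same with centre (0.54 and 1.08 points) as without (0.53 and 1.09). A reader might also infer that the open-label design lets someone pick a favourable seed, but section {17a} says data analysts are blinded.

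**Conclusion.** The point holds as a minor one. The number ten is stated. If the primary outcome is imputed, it leaves avoidable seed noise in the limit that decides non-inferiority: SD about 0.5 points at 5% missing outcomes, 1.1 points at 15%, and 0.2 to 0.4 points at 1 to 2%. Opposite verdicts from two seeds would occur in about 3 to 5% of trials at 5 to 15% missing, against about 1 to 2% with 100 imputations.

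This rests on four assumptions: the outcome is among the imputed variables, the verdict is read from the Rubin-pooled limit, outcomes are missing at random, and the true rates are those used for planning. The missing rate is assumed throughout. A reader might infer that the result of this trial is likely to turn on the seed. The figures do not support that: it can do so only when the limit lies within about 1 to 2 points of the margin.

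**What to change.** In section {20c}, or in the analysis plan with a cross-reference, change the number of imputations from ten to at least 100, run from one seed recorded before database lock, and report the Monte Carlo error of the lower limit with the primary result. In the same sentence, state whether the primary outcome is among the imputed variables. Leave the listed predictors, "the allocation group, the center, and the baseline condition", as they are.

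The cost is one sentence and a few minutes of computing, with no new data. Going from ten to 100 cuts the seed noise by about two thirds (1.09 to 0.33 points at 15% missing, 0.53 to 0.17 at 5%). The article describes recruitment as still open, so the change could be made before database lock.

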### Plans to give access to the full protocol, participant-level data, and statistical code {31c}

Dissemination of results directed to patients will be channeled through the Spanish Agency for Medicines and Health Products, and their content will be adapted to patients.

## Oversight and monitoring

### Composition of the coordinating center and trial steering committee {5d}

The *steering committee (SC)* will be the ultimate decision-making body of the FOVOCIP consortium and will be composed of the project coordinators ([name] and [name]) plus one representative of each participating institution. SC will meet at least once a year. Coordinators will chair SC meetings. Decision-making will be made based on consensus.

The *executive board* (EB) will be responsible for the overall strategic and technical management and will report directly to the SC. The EB will be comprised of the project coordinators plus 2 additional PIs of different centers participating in the study (elected by voting in the first SC meeting) plus the project monitor (PM) and the project assistant (PA). EB will execute the decisions of the SC as well as monitor the effective and efficient implementation of the project. Minutes of the EB meetings, once accepted, will be sent to the SC members in order to keep them informed. The coordinators will chair the EB meetings. The EB will meet at least quarterly and upon justified written request of any member of the EB.

*The management team* will support the PI and coPI coordinators in the day-to-day operational management and fulfilling the project’s administration tasks. The management team will comprise the PM of the IDIVAL and a full-time project assistant (PA) employed by the research team.

Finally, PIs in each center are responsible for including identifying potential recruits and taking consent.

### Composition of the data monitoring committee, its role and reporting structure {21a}

A meeting will be held by non-study personnel to evaluate the results of 80 patients. The interim analysis committee will be composed of a hematologist, a microbiologist and a clinical pharmacologist.

### Adverse event reporting and harms {22}

The investigators will be responsible for collecting all the adverse events in the clinical history based on those referred by the patient spontaneously or by interview during the follow-up visits. The causality of the adverse event related to the intervention will be evaluated and recorded in the clinical history and in the eCRF.

The investigators will report to the sponsor all serious adverse events occurring to subjects treated in the clinical trial, without undue delay, but not later than within 24 h of obtaining knowledge of the events.

The sponsor will report to the Spanish Agency for Medicines and Health Products all relevant information about suspected unexpected serious adverse reactions to investigational medicinal products occurring in this clinical trial.

### Frequency and plans for auditing trial conduct {23}

The CRA is a person independent of the research team who is not involved in patient recruitment and follow-up.

The local CRA makes a start-up and closing visit to each site. A first visit will take place in each center 30 days after the inclusion of the first patient. Subsequently, 4 to 6 visits will be performed per site, with a frequency of 1 visit every 4 months.

During the monitoring visits, 100% of the informed consents form, selection criteria, events and adverse reactions, and main and secondary variables (neutrophil counts, fever, study treatment, stored samples) will be reviewed. The remaining the variables will be reviewed every 5 patients.

### Plans for communicating important protocol amendments to relevant parties (e.g., trial participants, ethical committees) {25}

All notifications defined as relevant or non-relevant amendments will be made to the Spanish Agency for Medicines and Health Products and to the Ethics Committee of reference in accordance with Spanish legislation on clinical trials RD 1090/2015 of December 4. These decrees regulate clinical trials with medicinal products: the Ethics Committees for Research with medicines and the Spanish Registry of Clinical Trials.

